In June 2022, NICE also updated the guidelines on familial breast and ovarian cancer removing the recommendation against proactive assessment of breast cancer risk in general practice. This change was supported by a stakeholder consultation and opens up the potential for a general practice-based screening programme to identify those at above-population level risk of breast cancer rather than requiring women to self-present with concerns. This approach misses most women estimated to be at higher risk and increases inequalities [11]. A review of the literature against the consolidated framework for screening found that proactive risk assessment in general practice currently satisfies many of the standard principles for screening for women under 50 years [12]. However, while studies have demonstrated general acceptability (according to Sekhon et al [13]) and enthusiasm for assessing risk within general practice, previous research with the CanRisk tool has highlighted the need to tailor its development and use to the specific needs of general practice [14]. Research has also identified potential challenges to implementation, including the time needed to complete the assessment, IT requirements, competing demands and priorities, and training of staff [15]. It is not known whether multifactorial risk assessment will be acceptable to women within general practice or what the expected uptake would be and, despite rapid advances in understanding of the PGS contribution to risk assessment, few studies have attempted to implement PGS analysis within a general practice setting.

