## Aims and objectives

The overall aims of this study are to evaluate the feasibility, acceptability and psychological impact of proactively offering multifactorial breast cancer risk assessment incorporating PGS using CanRisk in general practice, and to collect estimates of outcomes and data on costs and healthcare utilisation. The latter will inform the design of a future trial and a health economic analysis to model the estimated reductions in breast cancer incidence and mortality if proactive breast cancer risk assessment using CanRisk were to be introduced in general practice across the UK.

Specific objectives:

To quantify uptake of proactive multifactorial breast cancer risk assessment using CanRisk in general practice amongst women under 50;To assess the acceptability of all stages of proactive multifactorial breast cancer risk assessment using CanRisk within general practice from the perspective of women, GPs, and staff in General Practice.To compare the number of women identified as at moderate or high risk of breast cancer following proactive multifactorial breast cancer risk assessment with those identified through routine care and the number expected from population-based studies;To quantify the psychological and behavioural impact of proactive multifactorial breast cancer risk assessment using CanRisk in general practice amongst women;To quantify the amount of data collected via the MyCanRisk public-facing data collection tool within a general practice population;To estimate the distribution of breast cancer risk amongst women under age 50 taking up the opportunity for multifactorial risk assessment following proactive invitation and uptake of risk-reducing interventions amongst those at moderate or high risk to inform sample size calculations for the design of a future randomised controlled trial;To estimate differences in uptake of proactive multifactorial breast cancer risk assessment and breast cancer risk distribution of women between general practices to inform the design and sample size calculations for a future cluster-randomised controlled trial;To collect data to enable estimation of the cost of delivering proactive multifactorial breast cancer risk assessment using CanRisk within general practice.

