### Processes and interventions

#### Practice recruitment.

GP practice recruitment was supported by the Clinical Research Network (CRN) Eastern. They approached practices across Cambridgeshire and Peterborough that refer patients at increased risk of developing breast cancer to the clinical genetics service at the Cambridge University Hospital NHS Foundation Trust. Practices were recruited from different areas to maximise participant sociodemographic and ethnic diversity. Practices that agree to take part signed a practice agreement form. Reasons for practices declining to take part in the study were collected where possible.

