## Study outcomes and measures

The study aims to generate data on the following outcomes:

Uptake of multifactorial breast cancer risk assessment, including the proportion of those invited who consent and the proportion of those invited who complete the breast cancer risk assessment, with or without the inclusion of the polygenic risk score.Distribution of breast cancer risk, including the proportion of women who consent who are at moderate or high risk on the initial CanRisk assessment in general practice (with or without the PGS) and those at moderate or high-risk following assessment in secondary/tertiary care.Proportion of women at moderate or high risk of breast cancer. The proportion of registered women aged 40–48 years at the start of the study at participating practices who are at moderate or high risk of breast cancer after assessment in secondary/tertiary care will be compared with the proportion of women aged 40–48 years at moderate or high risk of breast cancer after referral to secondary/tertiary care at non-participating practices across Cambridgeshire and Peterborough during the same time period, and also compared with the proportion of registered women aged 40–48 years at participating practices in the 12 months prior to the study.Uptake of risk-reducing interventions, including the proportion of those at moderate or high risk who attend for a GP appointment, are referred to secondary/tertiary care, and take up enhanced screening and/or preventative medication.Completeness of risk factor information collected through MyCanRisk, including the presence of information completed for non-family history risk factors (e.g., height, weight, alcohol, women’s health) and the number of family members included in the pedigree.Change in psychological and behaviour measures (Table 2) following multifactorial breast cancer risk assessment at one month, three months, and six months after receiving the risk estimate.Acceptability of the pathway of proactive multifactorial risk assessment within general practice to women and GPs, including response rates and completion of questionnaires and the willingness for practices to take part.Costs and workload associated with delivery of proactive multifactorial risk assessment.

**Table 2 pone.0336902.t002:** Assessments.

Construct	Baseline	1 month	3 months	6 months

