
### Data collection

The data collection process is shown in Fig 2.

Participant baseline data is collected via an online questionnaire.

Participant level follow-up data is collected via participant questionnaires at 1, 3 and 6 months after receiving the results letter and from the GP electronic medical records 6 months after the last participant has received the results letter for all individuals who have consented to participate in the study. This includes coded entries relating to breast symptoms, breast cancer risk and, for those at moderate and high risk, uptake of risk-reducing interventions.

Practice-level aggregated data on the age, ethnicity and Index of Multiple Deprivation of all eligible women will be extracted at the end of the study from the GP electronic medical records. Practice-level and aggregated individual level data on the number of referrals of women potentially at above population-level risk for breast cancer and the outcomes of those referrals for all practices across Cambridgeshire and Peterborough for the period of the study will also be extracted from the electronic health records at the clinical genetics clinic at Cambridge University Hospitals NHS Foundation Trust. For the practices participating in this study, the same data will be extracted for the 12 months prior to the study. Data on the number of women registered at each practice will be extracted from publicly available National General Practice profiles.

A mixed-methods process evaluation is being conducted alongside collection of outcome data to explore how proactive breast cancer risk assessment is delivered and perceived at practice and patient levels. The main four questions guiding this element of the study will focus on: 1) whether this feasibility study did what it was set out to do; 2) whether the different elements in the study design worked and why; 3) what the different stakeholders thought about CanRisk and how it was implemented in general practice: and 4) whether implementing CanRisk in general practice is acceptable. Data is collected from women, GPs conducting breast cancer risk consultations, and practice managers and/or research leads from the different research sites. Three sources of data contribute to this process evaluation.

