### Sample size

Based on an uptake of 16% in the only study in the UK that invited women to complete a breast cancer risk assessment [35], we estimate that to recruit 1,000 women we need to invite approximately 5,000 women from across the GP practices.

Based on distributions of known risk factors in the UK, we estimate that approximately 17% (170) of those 1,000 women will be at above population-level risk [1]. This will allow us to estimate:

the proportion of eligible women in each practice who consent to take part in the study with an accuracy of +/- 1.1% (width of the 95% CI) based on an estimate of 20%the proportion of eligible women in each practice who consent who complete the risk assessment with an accuracy of +/- 2.5% based on an estimate of 80%the proportion of women who consent who are at moderate or high risk on initial CanRisk assessment in general practice with an accuracy of +/- 2.5% based on an estimate of 17%the proportion of those at moderate or high risk who attend for an appointment with a GP and who are referred to secondary/tertiary care with an accuracy of +/- 5.7% based on an estimate of 80%

Allowing for a 40% loss to follow-up, 1,000 participants will allow us to detect a change in anxiety or worry of 0.5 SD or greater at each time point at p < 0.05 and 90% power in both women at population level risk and in the subgroup identified at moderate or high risk. 1,000 participants will also allow us to detect an estimated increase in the proportion of registered women identified at moderate and high risk through proactive multifactorial risk assessment across all the participating practices compared with the 12 months prior to the study with a 95% confidence interval of +/- 0.005 (5 per 1,000 registered women).

Together with data on the acceptability of the proactive multifactorial breast cancer risk assessment, the following progression criteria will be evaluated to judge whether a subsequent full trial of proactive multifactorial breast cancer risk assessment would be feasible: 16% uptake into the study; 60% response to follow-up questionnaires; 80% of women receiving their breast cancer risk and offered subsequent risk management advice/referral. If any of those criteria are not met, we will use the data from the process evaluation to adapt the approach for subsequent feasibility and/or pilot studies before consider progressing to a subsequent full trial.

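### Pre-study referral data are planned only for participating practices, so the data cannot separate both a baseline practice difference and a time trend from the effect

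*Protocol article*

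**What the plan says.** The objective (protocol article, Aims and objectives) is to compare the number of women found at moderate or high risk "with those identified through routine care and the number expected from population-based studies".

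Study outcomes and measures turns the routine-care part into two comparisons for registered women aged 40–48 years. One is concurrent, against women found at that risk level "after referral to secondary/tertiary care at non-participating practices across Cambridgeshire and Peterborough during the same time period". The other is before-after: "and also compared with the proportion of registered women aged 40–48 years at participating practices in the 12 months prior to the study".

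Data collection fixes what is extracted. Referral numbers and outcomes "for all practices across Cambridgeshire and Peterborough for the period of the study will also be extracted from the electronic health records" of the regional genetics clinic. The earlier period is narrower: "For the practices participating in this study, the same data will be extracted for the 12 months prior to the study".

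On how practices joined, Practice recruitment describes an approach through the research network to practices that refer to the Cambridge genetics service, agreement by those willing, and a spread of areas: "Practices were recruited from different areas to maximise participant sociodemographic and ethnic diversity".

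Sample size gives a precision for the before-after comparison only: "compared with the 12 months prior to the study with a 95% confidence interval of +/- 0.005 (5 per 1,000 registered women").

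**The concern.** There are two types of practice and two periods, so four cells. The plan fills three: participating before, participating during, and non-participating during. The empty one is non-participating before.

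Practices that agreed to join, and that were chosen for spread of area, may have had different identification rates from the rest of the region before the study began. The concurrent comparison would carry that difference into its result. Identification through routine care may also drift from one year to the next, and the before-after comparison would carry that drift. Each comparison needs an assumption that the planned data cannot check. Because the gap is in what is extracted, no later analysis plan can close it.

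At stake is how far the estimate for this objective can be attributed to the proactive offer.

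**Working it through.** **Step 1. The plan's own figure.** Inputs from Sample size: about 5,000 invited, 1,000 recruited, 17% (170) above population-level risk. Taking the 5,000 as the registered women, p = 170/5,000 = 0.034.

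Half-width = 1.96 × √(0.034 × 0.966 / 5,000) = 0.00502.

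This reproduces the stated ±0.005. It is the sampling error of the study-period proportion alone. Adding the prior-year proportion, with p0 not given and assumed to be 0.001 to 0.01 on the same 5,000, gives 0.0051 to 0.0057. Neither figure contains any allowance for bias.

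**Step 2. What three cells can identify.** Let r be the pre-study rate at non-participating practices, d the baseline difference of participating practices, t the change over time, and e the effect.

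| | Before | During |
|---|---|---|
| Participating | r + d | r + d + t + e |
| Non-participating | r (not extracted) | r + t |

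- Concurrent: (r + d + t + e) − (r + t) = e + d.
- Before-after: (r + d + t + e) − (r + d) = e + t.
- Gap between the two: d − t.

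Three observed cells and four unknowns leave e unidentified (the design matrix has rank 3 for 4 parameters). With the fourth cell the rank is 4, and (e + t) − t = e, provided that t is the same in both groups of practices.

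**Step 3. Whether other planned data fill the gap.** Data collection also takes age, ethnicity and deprivation of eligible women from GP records. These describe case mix and do not measure earlier referral or identification. Practice list sizes from public profiles supply denominators only.

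**Step 4. Size.** The increase implied by the plan, if all registered women are invited:
- 170/5,000 = 34 per 1,000 identified on initial assessment;
- 170 × 0.80 = 136, and 136/5,000 = 27 per 1,000 after the plan's 80% attending a GP and being referred.

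The article gives no routine rate, so d and t have to be assumed. A routine rate of 2 per 1,000 that is out by a factor of 1.5 gives 2 × 0.5 = 1 per 1,000. A rate of 5 per 1,000 that is out by a factor of 2 gives 5 × 1 = 5 per 1,000. Against the implied increase:
- 1/34 = 3%;
- 5/27.2 = 18%.

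Participant recruitment allows a random sample of eligible women to be invited, while the outcome's denominator stays all registered women. If half were invited, 5,000 invitations would come from 10,000 women and the implied increase would be 13.6 to 17 per 1,000. The same bias would then be 1/17 = 6% to 5/13.6 = 37%.

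**Step 5. Precision after the fix.** With p1 = 0.034 and n = 5,000 in each participating cell, p0 assumed to be 0.001 to 0.01, and an assumed 20,000 to 100,000 non-participating women (N):

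Half-width = 1.96 × √[p1(1 − p1)/5,000 + p0(1 − p0)/5,000 + 2 × p0(1 − p0)/N] = 0.0051 to 0.0061,

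against 0.0051 to 0.0057 for the simple before-after difference. Both ignore clustering across the 5–8 practices, which would widen all of these intervals.

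**The case against.** The strongest defence is that two imperfect controls with different weaknesses are a recognised design. Their gap is d − t, so close agreement would leave a shared bias only if two unrelated distortions happened to match. If d and t have opposite signs, the two estimates bracket the effect. Two routine rates will be observed, and if both prove very low there is little room for bias. The objective also names a third benchmark, from population-based studies. All of this stands. It limits the damage but does not identify the effect when the two estimates differ, or when d and t share a sign.

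A reader might infer that the article itself documents a trend between the two periods, since the Introduction reports that "NICE also updated the guidelines on familial breast and ovarian cancer removing the recommendation against proactive assessment of breast cancer risk in general practice". The documents do not support this. That change is dated June 2022. Recruitment opened on 28 November 2024, so the prior 12 months begin around November 2023 and both periods fall after it. A slow drift is possible, but none is shown.

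It is also tempting to say that the missing cell would remove both biases. It does so only under parallel trends, which one pre-study period cannot test.

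Finally, the article's Analysis section has no part on this comparison, and adjustment may be set out in a full protocol or analysis plan that is not shown. That is fair for the analysis. The extraction scope, however, is stated in the article.

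**Conclusion.** The point holds as a limited, inexpensive improvement. The planned data fill three of four cells for non-randomised practices, so a baseline difference and a time trend cannot both be separated from the effect.

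The size of the bias is unknown. The 3% to 18% rests on an assumed 1 to 5 per 1,000, on 136 to 170 women out of 5,000, and on all registered women being invited. A reader might set the same 1 to 5 against the stated ±5 per 1,000 and conclude that the bias rivals the precision. That range is assumed, and the increase being estimated is the more relevant yardstick.

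Nor do the documents support reading this as a failure of the study. It is a feasibility study, the comparison is one of eight outcomes, and the progression criteria are uptake, questionnaire response, and women receiving their risk and advice. If routine rates are about 2 per 1,000 or lower, the bias would be small against the implied increase.

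**What to change.** - **Data collection:** extract the same referral and outcome data for the 12 months before the study for the non-participating comparator practices as well as the participating ones.
- **Study outcomes and measures:** keep the two planned comparisons and add a difference-in-differences estimate beside them (change at participating practices minus change at non-participating practices). Express all rates on a common time base, because the study period need not be 12 months long, and state the parallel-trends assumption.

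The cost is a wider date range in a clinic-record extraction already planned for every practice, with no participant contact. The sponsor may need to check that approvals cover the earlier records of non-participating practices, since the article does not say. The interval becomes slightly wider: a half-width of 0.0051 to 0.0061 against 0.0051 to 0.0057, on the assumptions above.

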#### Questionnaires.

The baseline questionnaire for women includes questions covering participants’ motivations and concerns regarding their participation in the study and its prospective acceptability [26]. The one-month follow-up questionnaire for those advised to have a consultation with their GP includes questions to assess participants’ views on the usefulness of the consultation, and whether the appointment clarified their understanding of breast cancer risk. The three month follow-up additionally includes questions about retrospective acceptability [26]. All GPs taking part in this study will be invited to complete an electronic questionnaire after the study. The questionnaire includes questions around acceptability [26] and from the NoMAD checklist about the potential for the intervention to be incorporated into practice [34]. One practice manager and/or research lead per research site will also be invited to complete the NoMAD survey completed by GPs.

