Table 1 shows the risk cut offs for near population risk, moderate risk and high risk for lifetime risk (defined as the risk between the ages of 20 and 80), and 10 year risk between the ages of 40 and 50.[7] For women falling in different categories based on the two definitions of risk, whichever is highest determines the risk category (i.e., near population risk, moderate and high risk) they will be classified as for the purposes of implementing current NICE guideline [7].

A list of women advised to make an appointment with their GP is sent to practices each month. Any women who have not booked a consultation or already consulted with a GP is contacted by practice staff and supported to book an appointment if they wish. Each patient contact and any reasons for not wishing to consult with a GP is recorded by the practice staff.

The process for returning results to participants and subsequent management is shown in Fig 2.

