**Outcomes**				
Risk perception				
Breast cancer risk perception (absolute)	•	•	•	•
Breast cancer risk perception (comparative)	•	•	•	•
Breast cancer risk conviction	•	•	•	•
Recall of risk information		•	•	•
Psychological				
Anxiety [22]	•	•	•	•
Cancer-specific worry [21]	•	•	•	•
Quality of life [24]	•	•	•	•
Impact of cancer risk assessment [27]		•	•	•
Satisfaction with test		•		
Views on the risk information [33]		•		
Attitude towards risk management options		•	•	•
Lifestyle and behavioural				
Current behaviour (breast self-examination)	•	•	•	•
Intention to attend screening	•	•	•	•
Change in behaviour (weight, alcohol consumption, exercise)		•	•	•
Healthcare utilisation	•			•
Actions following risk assessment (moderate/high risk or those with additional risk factors)				
Consultation with GP (or intention if not done)		•	•	•
Uptake of risk reduction strategies (or intention if not done)				
Enhanced screening		•	•	•
Risk reducing medication		•	•	•
Surgery		•	•	•
Process evaluation				
Acceptability [26]	•		•	
Motivations and concerns	•			
Views on GP consultation (only for moderate/high risk or those with additional risk factors)		•		

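### Views on the GP consultation are collected by questionnaire only at 1 month after the results letter, so the questionnaire estimate describes early attenders only

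*Protocol article*

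**What the plan says.** The Questionnaires section of the protocol article assigns the consultation questions (how useful it was, and whether it made the woman's risk clearer to her) to "The one-month follow-up questionnaire for those advised to have a consultation with their GP". Table 2 lists "Views on GP consultation (only for moderate/high risk or those with additional risk factors" as a process evaluation item with one mark, in the 1-month column.

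Data collection times the follow-up from the letter, not from the consultation: "participant questionnaires at 1, 3 and 6 months after receiving the results letter".

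The section on risk categorisation and returning results describes how women are brought to the consultation. "A list of women advised to make an appointment with their GP is sent to practices each month", and then "Any women who have not booked a consultation or already consulted with a GP is contacted by practice staff" and helped to book if they wish.

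Attendance is followed for longer than opinion. Table 2 marks "Consultation with GP (or intention if not done" at 1, 3 and 6 months. The only process evaluation content added later is general: "The three month follow-up additionally includes questions about retrospective acceptability". The text above the Data collection section presents Table 2 as the full specification of measures and time points, so the single mark is a stated choice and not something left out of a condensed article.

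**The concern.** The opinion item is tied to a fixed date after the letter, while the event it asks about has no fixed date. A woman whose letter goes out just after a list has been sent may first be contacted by her practice almost a month later, and booking and being seen take further time. She can report at 3 or 6 months that she has consulted, but neither questionnaire then asks what she thought of it.

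The second objective is the acceptability of every stage of the pathway to women, and the Sample size section weighs acceptability data alongside the progression criteria. The consultation is the step that every woman with an above-population result, or with additional family-history features, is advised to take. If the questionnaire result on it comes only from women seen within about a month, it does not describe everyone who attended. The practice contact process is itself part of what the study is testing, and some of the women it brings in will be among those not asked.

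**Working it through.** The plan states no figure on this point, so there is none to reproduce. The check sets the schedule against the pathway and then gives a scale.

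**1. Schedule against pathway**
- Views on the consultation: 1 month only (Table 2; Questionnaires).
- Attendance at the consultation: 1, 3 and 6 months (Table 2).
- Start of the clock: receipt of the results letter (Data collection).
- Contact with women who have not booked or consulted: from a monthly list (Risk categorisation and returning risk assessment results).

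The attendance row shows that the plan foresees consultations after 1 month. The views row has no counterpart for them.

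**2. Could the monthly contact process produce late consultations?**

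The documents give no booking delay, so this step is illustrative. Assume that letters are spread evenly over a 30-day list cycle, and that a contacted woman is seen *d* days after the first list on which she appears. The wait from letter to list is then uniform on 0 to 30 days. She is seen after day 30 if that wait exceeds 30 − *d* days, which has probability *d*/30:
- *d* = 7: 7/30 = 23%
- *d* = 14: 14/30 = 47%
- *d* = 21: 21/30 = 70%
- *d* = 28: 28/30 = 93%

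These shares apply to women contacted from the list, not to all attenders. Late consultations are plausible at any realistic delay, but not every contacted woman is late.

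**3. How many women?**

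Inputs from the Sample size section: 170 women above population-level risk; 80% attending; 60% response to follow-up questionnaires (the progression criterion, which matches the 40% loss allowed for).
- Expected attenders: 0.80 × 170 = 136. Women near population risk with additional family-history features would add to this.
- Late share *L* is not in the documents; 10% to 50% is assumed.
- Late attenders = *L* × 136: 10% gives 14, 25% gives 34, 50% gives 68.
- Late attenders who would have responded = 0.60 × *L* × 136: 10% gives 8, 50% gives 41.
- Early attenders left to answer at 1 month = 0.60 × (1 − *L*) × 136: 10% gives 73, 25% gives 61, 50% gives 41.

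**4. Can the other sources reach late attenders?**
- Optional survey straight after a recorded appointment: 20 recordings planned, so at most 20/136 = 15% of attenders.
- Interviews on the whole pathway: up to 30 women, so at most 30/136 = 22%, and fewer in practice because they span all risk levels. A follow-up interview up to six months later is optional.

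Both can reach some late attenders. Both are small and depend on volunteering.

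**The case against.** Nothing is misstated: the text and Table 2 agree. The item is one descriptive row in a mixed-methods process evaluation. It feeds no progression criterion on its own, no powered comparison and no precision target. A single early measurement is a defensible trade-off between burden and recall. The survey after recorded appointments is timed from the consultation, so lateness does not affect it, and the follow-up interviews are meant for later parts of the pathway. The 3-month acceptability questions also reach women seen between 1 and 3 months. All of this stands and limits the weight of the point. It does not close the gap: the survey and interviews are small and voluntary, and the 3-month questions are not about the consultation.

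A reader might infer more than the documents support, in four ways:
- *That late attenders are never asked.* The recorded-appointment survey and the interviews can reach some of them.
- *That only unprompted women are covered.* A woman listed a few days after her letter can be contacted and seen within the month. Conversely, a woman who books at once but gets a late slot misses the item without being hesitant at all.
- *That the result will look too favourable.* Nothing in the documents shows how later attenders rate their consultations.
- *That information on barriers to attending is lost.* This item asks about usefulness and understanding. Barriers are sought elsewhere: practices record reasons for not wishing to consult, intention is asked at each follow-up, and interviews with women who decline or do not complete parts of the study are planned where possible.

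**Conclusion.** The point holds as a gap in coverage. Followed as written, the plan gives questionnaire data on the consultation only for women seen before they complete the 1-month questionnaire, although it expects and records later attendance. The result should not be read as the view of all attenders.

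The size is uncertain. The range of 14 to 68 women out of 136, or about 8 to 41 at 60% response, rests on an assumed late share of 10% to 50%. It also takes the plan's 80% attendance at face value and applies the 60% threshold to this subgroup. The documents give no late-attendance rate and no completion window for the 1-month questionnaire. The gap itself does not depend on the exact share. The direction of any bias cannot be determined from the documents. This is a modest measurement weakness in a stated objective that is worth correcting because it is cheap to correct; it does not threaten the study.

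**What to change.** Show the existing consultation items in the 3-month and 6-month questionnaires to any woman who reports a consultation and has not yet answered them. Report the views by time from results letter to consultation, so that early and later attenders can be seen separately.

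Recruitment was due to close on 30 June 2025, so some or all of this follow-up may have passed. In that case, use the 3-month and 6-month attendance answers to report how many attenders consulted after their 1-month questionnaire, restrict the questionnaire conclusion to early attenders, and say which recorded-appointment surveys and interviews came from later attenders.

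The cost is a branching rule, a minor amendment and a few extra items for a subset of women. The interval between consultation and answer will vary more, which is a further reason to report by timing. No visit is added and clinical management does not change.
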